## Abstract

**Background:**

The COVID-19 pandemic is expected to cause significant morbidity and mortality. The development of an effective vaccine will take several months to become available, and its affordability is unpredictable. Transfusion of convalescent plasma (CP) may provide passive immunity. Based on initial data from China, a group of hematologists, infectious disease specialists, and intensivists drafted this protocol in March 2020.

**Objective:**

The aim of this study is to test the feasibility, safety, and efficacy of CP in treating patients with COVID-19 across Saudi Arabia.

**Methods:**

Eligible patients with COVID-19 will be recruited for CP infusion according to the inclusion criteria. As COVID-19 has proven to be a moving target as far as its management is concerned, we will use current definitions according to the Ministry of Health (MOH) guidelines for diagnosis, treatment, and recovery. All CP recipients will receive supportive management including all available recommended therapies according to the available MOH guidelines. Eligible CP donors will be patients with COVID-19 who have fully recovered from their disease according to MOH recovery criteria as detailed in the inclusion criteria. CP donors have to qualify as blood donors according to MOH regulations except for the history of COVID-19 in the recent past. We will also test the CP donors for the presence of SARS-CoV-2 antibodies by a rapid test, and aliquots will be archived for future antibody titration. Due to the perceived benefit of CP, randomization was not considered. However, we will compare the outcome of the cohort treated with CP with those who did not receive CP due to a lack of consent or lack of availability. In this national collaborative study, there is a likelihood of not finding exactly matched control group patients. Hence, we plan to perform a propensity score matching of the CP recipients with the comparator group patients for the major characteristics. We plan to collect demographic, clinical, and laboratory characteristics of both groups and compare the outcomes. A total sample size of 575 patients, 115 CP recipients and 460 matched controls (1:4 ratio), will be sufficient to detect a clinically important hospital stay and 30-day mortality difference between the two groups with 80% power and a 5% level of significance.

**Results:**

At present, patient recruitment is still ongoing, and the interim analysis of the first 40 patients will be shared soon.

**Conclusions:**

In this paper, we present a protocol for a national collaborative multicenter phase II study in Saudi Arabia for assessing the feasibility, safety, and potential efficacy of CP in treating patients with severe COVID-19. We plan to publish an interim report of the first 40 CP recipients and their matched comparators soon.

**Trial Registration:**

ClinicalTrials.gov NCT04347681; https://clinicaltrials.gov/ct2/show/NCT04347681

**International Registered Report Identifier (IRRID):**

PRR1-10.2196/23543

## Introduction

### Background

The COVID-19 pandemic, caused by SARS-CoV-2, is a major health and economic concern worldwide due to its morbidity and mortality. Coronaviruses are a large family of RNA viruses that cause illnesses ranging from the common cold to more severe diseases such as Middle East respiratory syndrome–related coronavirus (MERS-CoV) and severe acute respiratory syndrome–related coronavirus (SARS-CoV) [1]. The new strain of coronavirus identified in December 2019 in Wuhan City, Hubei Province of China was called the 2019 novel coronavirus. The International Committee on Taxonomy of Viruses determined that SARS-CoV-2 is the same species as SARS-CoV. The World Health Organization (WHO) has named the disease associated with SARS-CoV-2 infections COVID-19.

Clinical features of SARS-CoV-2 infection typically include fever and respiratory symptoms like cough and shortness of breath; in severe cases, the infection can cause pneumonia, severe acute respiratory distress syndrome (ARDS), kidney failure, and even death. SARS-CoV-2 has a higher transmission rate with an approximate fatality rate of 3% [2]. The final diagnosis of SARS-CoV-2 infection depends on laboratory detection of the SARS-CoV-2 viral RNA by real-time reverse transcription–polymerase chain reaction (rRT-PCR) [1-4].

The concept of using convalescent plasma (CP) is not new since it has been tried in limited numbers of patients during recent viral crises, including the 2003 severe acute respiratory syndrome epidemic, the 2009 “swine flu” epidemic, and the 2012 outbreak of Middle East respiratory syndrome [5]. CP treatment reduced mortality in patients with severe pandemic influenza A 2009 virus infection [6]. Patients with a resolved viral infection typically develop a polyclonal antibody immune response to different viral antigens. Some of these polyclonal antibodies will likely neutralize the virus and prevent new rounds of infection. Patients who recovered from COVID-19 can donate plasma, and then, this plasma can be transfused into patients who are actively infected [7]. Indeed, the same rationale was used in the treatment of several patients with Ebola with convalescent serum during the outbreak in 2014-2015 [8].

Therefore, CP therapy is expected to improve the clinical, laboratory, and radiological features of the patients severely affected by COVID-19. Decreasing the morbidity and mortality of COVID-19 in a cost-effective manner, leading to improved quality of health care and self-sufficiency in the treatment of serious diseases affecting the masses, is in line with the top priorities in Vision 2030 of the Kingdom of Saudi Arabia.

### SARS-CoV-2–Specific Immunoglobulins Containing CP

Among the most attractive intuitive options, during this fast-kinetic pandemic, is treating the patients who are sick with COVID-19 with SARS-CoV-2–specific immunoglobulins found in patients who have fully recovered from COVID-19 and are considered no longer infected. We know from prior research that antibodies against viral antigens render people immune, but we do not know yet how long the immunity will last. However, Zhao et al [9] showed seroconversion in 173 patients with COVID-19 appeared for total antibody, immunoglobulin M (IgM), and immunoglobulin G (IgG) at 11, 12, and 14 days [9]. The presence of antibodies was <40% in the first 7 days and then rapidly increased to 100%, 94.3%, and 79.8% for antibodies, IgM, and IgG, respectively, by day 15. In contrast, viral RNA decreased from 66.7% before day 7 to 45.5% in days 15-39. Moreover, a higher titer of antibodies was independently associated with clinically worse COVID-19 (*P*=.006) [9].

### Antibodies Detection by a Rapid Serological Method and Their Kinetics

In those patients who have passed the viremic phase, the presence of antibodies is highly desirable and provides evidence of the immunity to combat COVID-19 (Table 1). Fortunately, the Saudi Food and Drug Authority (SFDA) has recently approved a needed rapid test kit made by BIOZEK company and other brands in the Saudi market that qualitatively detect IgG and IgM antibodies against SARS-CoV-2 from whole blood, serum, or plasma using a single-use cassette. This kit uses lateral flow chromatographic immunoassay and can produce results within 10 minutes. The combination use of the IgM and IgG tests can reflect virus infection and the immune status of the body effectively (Table 1).

**Table 1 table1:** How to interpret the results of PCR and antibody results.^a^

Test results			Clinical Significance	
PCR^b^	IgM^c^	IgG^d^		
✓^e^	—^f^	—	The patient may be in the window period of infection.	
✓	✓	—	The patient may be in the early stage of infection.	
✓	✓	✓	The patient is in the active phase of infection.	
✓	—	✓	The patient may be in the late or recurrent stage of infection.	
—	✓	—	The patient may be in the early stage of infection. PCR result may be false-negative.	
—	—	✓	The patient may have had a past infection and has recovered.	
—	✓	✓	The patient may be in the recovery stage of an infection, or the PCR result may be false-negative.	

^a^Adapted from [10,11].

^b^PCR: polymerase chain reaction.

^c^IgM: immunoglobulin M.

^d^IgG: immunoglobulin G.

^e^Indicates a positive result.

^f^Indicates a negative result.

### Role of CP in Treating Severe COVID-19

Casadevall and Pirofski [12] suggested that convalescent sera from individuals with COVID-19 may be an option for treating the highest-risk patients with COVID-19 and possibly for prophylaxis of infection in individuals at high risk of COVID-19. This passive antibody administration concept to prevent disease is already used in patients exposed to hepatitis B and rabies viruses, and to prevent severe respiratory syncytial virus disease in high-risk infants [12]. The proposed use of convalescent sera in the COVID-19 epidemic would rely on preparations of high titers of neutralizing antibodies against SARS-CoV-2.

In the first pilot Chinese study reported by Duan et al [13], CP therapy in 10 patients showed a potential therapeutic effect and low risk in the treatment of patients with severe COVID-19. One dose of CP with a high concentration of neutralizing antibodies can rapidly reduce the viral load and tends to improve clinical outcomes [13]. The optimal dose and treatment time point, as well as the definite clinical benefits of CP therapy, need to be further investigated in randomized clinical studies. Out of 40 donors (recovered patients with COVID-19), 39 showed a high antibody titer of at least 1:160. After receiving CP therapy, 9 out of 10 recipients were found to have neutralizing antibody titers >1:640 [13]. Although small, it is a pivotal study to prove the safety and efficacy of CP therapy. All patients showed an increase in oxygen saturation within 3 days. Other parameters that improved were increased absolute lymphocyte counts (ALCs) and decreased C-reactive protein (CRP). Varying degrees of resolution of lung lesions were also seen on radiological examinations within 7 days. In 7 patients who previously had viremia, the viral load was undetectable after transfusion [13].

### Currently Available Therapeutic Options for COVID-19

According to the WHO, the management of COVID-19 has mainly focused on infection prevention, case detection, monitoring, and supportive care, although there are reports on the efficacy of new potential therapeutic agents (Figure 1). However, no specific anti–SARS-CoV-2 treatment is recommended because of conflicting evidence. Evidence shows that CP from patients who have recovered from viral infections can be used as a treatment without the occurrence of severe adverse events (SAE). Therefore, it might be worthwhile to test the safety and efficacy of CP transfusion in patients infected with SARS-CoV-2 [14].

Our study aims to test the feasibility, safety, and efficacy of CP in treating patients with COVID-19 across Saudi Arabia.

**Figure 1 figure1:**
[figure not shown]
Some therapeutic options for treating COVID-19.

## Methods

This is a national, phase II, multicenter trial evaluating the safety and potential efficacy of CP to treat severe COVID-19 and patients at high risk of developing severe COVID-19. Detailed bilingual informed consent forms (ICFs) approved by the Ministry of Health (MOH) and institutional review boards (IRBs) will be used for both CP donors and CP recipients.

### Time of the Study

The proposed duration of 3 months was considered ideal for recruiting the first 40 CP recipients for our proposed prospective study. If interim analysis shows the benefit of CP, we will increase the sample size and extend the trial period.

### Inclusion Criteria

The inclusion criteria for recipients is as follows:

18 years or olderPatients with COVID-19 confirmed by positive rRT-PCR test for SARS-CoV-2 “using one of the SFDA approved kits used in the Kingdom of Saudi Arabia” as per current MOH guidelinesMust have required intensive care unit (ICU), severe, or immediately life-threatening care:Patient requiring ICU care or admissionSevere disease is defined as dyspnea, respiratory frequency≥30/min, blood oxygen saturation≤93%, the partial pressure of arterial oxygen to fraction of inspired oxygen ratio<300, or lung infiltrates>50% within 24-48 hours.Life-threatening disease is defined as respiratory failure, septic shock, or multiple organ dysfunction or failure.

The inclusion criteria for the donors was as follows:

18 years or olderPrior confirmed COVID-19 diagnosis as per current MOH guidelinesComplete clinical recovery from COVID-19 before donation (at least 14 days from the last SARS-CoV-2 negative polymerase chain reaction or 28 days from the initial symptoms) [15-18]All MOH criteria for blood donation will be followed.All transfusion transmissible infections markers on the donor’s blood are negative as per current MOH routine blood donor screening regulations.Positive rapid serology test for antibodies (IgG) against SARS-CoV-2 indicating immunity against COVID 19

### Exclusion Criteria

The exclusion criteria for recipients was a negative or nonconclusive COVID-19 rRT-PCR test for SARS-CoV-2, mild symptoms, and hospitalization not requiring ICU care or admission. The exclusion criteria for donors was being unfit for blood donation or a multiparous or pregnant female.

### Collection of CP Infusion for Treatment of COVID-19

As antibody kinetics show IgG levels are highest around day 28 and decline around day 42 to complete disappearance in many months, we will try to get plasma donation from fully recovered patients soon after day 28 of the onset of symptoms (that usually last for 7-10 days). For the recovery definition, we will continue to follow the MOH’s current precautionary protocol to prevent the spread of the virus causing COVID-19 that requires blood donor abstinence from donation for 28 days from exposure [17,18].

Plasmapheresis to collect plasma from the donors (using Trima, Hemonetics, or alike machines) is a commonly used procedure. Donors are required to be in an acceptable health state and pass through a multistep screening (donor history questionnaire, vital signs check, laboratory tests, etc) before CP donation. The arrangement for plasmapheresis and collection will start after obtaining the donor’s informed consent. The collected plasma will undergo an additional safety step of pathogen reduction using Mirasol or Intercept Pathogen Reduction Technology, which is SFDA and CE (Conformité Européenne) approved (Figure 2). The Mirasol system uses vitamin B2 (riboflavin) and ultraviolet light. Mirasol-treated fresh frozen plasma (FFP) maintains a good quality of therapeutic proteins as demonstrated in multiple external validation studies [19-21]. After passing through the pathogen reduction system, the CP will be sent to the COVID-19 recipients, or it can be stored in a dedicated FFP freezer at ≤–18 °C. The shelf life of frozen CP should be similar to normal FFP according to the storage conditions (1 year at ≤–18 °C or 24 hours at 1-6 °C). The CP units will be labeled, stored, and shipped as per Central Board for Accreditation of Healthcare Institutes (CBAHI), American Association of Blood Banks (AABB), and Joint Commission International guidelines for blood products handling and management.

CP will be used only for eligible patients who have COVID-19. The common side effects of FFP transfusion include side effects of blood product transfusion (eg, allergic or febrile reactions, transfusion-related acute lung injury [TRALI], and transfusion-associated circulatory overload [TACO]) while the infectious risk is minimal. Plasma volume to be collected from each donor can be up to 15% of the total blood volume (TBV; TBV = weight in kg x 70 ml). For example, from a CP donor who weighs 65 kg, we can collect up to ~682 ml plasma (15 / 100 x 65 x 70). CP donors can donate more than once as per the regulations of the CBAHI and AABB, which allows healthy donors to donate plasma twice in a month up to a maximum of 24 donations in a year. Special International Society of Blood Transfusion labels will be affixed on the plasma bags indicating COVID-19 CP (Figure 2).

**Figure 2 figure2:**
[figure not shown]
Logistic cycle of convalescent plasma procurement from donor, processing, and infusion to patient with COVID-19. IgG: immunoglobulin G; IgM: immunoglobulin M.

### ICF

The ICF will be used for both the CP donor and the recipient (Approved Donor ICF [Arabic and English] and Approved Recipient ICF [Arabic and English]).

### Transfusion of CP for Treatment of COVID-19

After obtaining informed consent, eligible patients who have severe COVID-19 and have not recovered yet will be infused with the donated CP 300 ml (200-400 ml/treatment dose) at least once and, if needed, daily for up to 5 sessions (Figure 3).

Other supportive and therapeutic measures should continue according to the locally approved protocols with due diligence. Patients will be monitored after FFP transfusion for the usual side effects of blood product transfusion (eg, allergic or febrile reactions, TRALI, and circulatory overload). We will then assess the response after the infusion of the plasma in these patients as detailed in the Response Assessment section.

As with other plasma therapies, attention should be given to ABO compatibility. For plasma selection, we will consider ABO compatibility (Table 2) regardless of Rh status. To minimize the risk of TRALI, preference will be given to plasma from male donors and nulliparous women.

**Figure 3 figure3:**
[figure not shown]
Schematic for the proposed process of CP donation and infusion. CP: convalescent plasma; PCR: polymerase chain reaction.

**Table 2 table2:** ABO group selection order for transfusion of plasma.^a^

Patient’s ABO group		Fresh frozen plasma
**O**		
	First choice	O
	Second choice	A or B
	Third choice	AB
**A**		
	First choice	A
	Second choice	AB
	Third choice	B^b^
**B**		
	First choice	B
	Second choice	AB
	Third choice	A^b^
**AB**		
	First choice	AB
	Second choice	A^b^
	Third choice	B^b^

^a^Adapated from [22].

^b^Tested and negative for high titer anti-A and/or anti-B (should be less than 1:64).

### Data Collection

Clinical information of all enrolled patients will be retrieved from the hospital electronic or paper records system, including the following:

Baseline demographic dataDays of illness durationPresenting symptomsRadiological findings (chest x-ray and computed tomography [CT] scan chest, if possible) on the day of hospital admission; on the day of ICU admission; on the day of CP infusion (day 0); and on days 3, 7, 14, and 30Laboratory infectious marker testing results like respiratory, urinary, or blood cultureLaboratory inflammatory markers: CRP (day of CP infusion [day 0] and then on days 3, 7, 14, and 30)Application of assisted mechanical ventilation and their modes, intranasal oxygen inhalation, number of days of intubation, or nasal oxygen supportMedication regimen (eg, hydroxychloroquine, azithromycin, any antiviral therapies, steroids, tocilizumab)Complications including acute renal failure, acute coronary syndrome, myocarditis, ARDS, gastrointestinal complication, and nosocomial infectionThe SARS-CoV-2 RNA from the serum sample will be monitored during treatment and at day 14 of recovery or discharge, whichever is later.

We plan to test for all of the following parameters for patients with COVID-19:

Complete blood count (CBC) differential to include percent and ALC, and percent and absolute neutrophil countChemistry panel to include total protein, albumin, lactate dehydrogenase, alanine aminotransferase and aspartate aminotransferase, and procalcitoninCardiac biomarkers (eg, cardiac troponins)Creatine phosphokinaseFerritinFull coagulation profile to include partial thromboplastin (PT), activated PT time, fibrinogen, and D-dimerCRPOxygen saturationRadiological examinationABO RhD grouping and antibody screeningrRT-PCR test for SARS-CoV-2Test for IgG and IgM antibodies against SARS-CoV-2

CP donors will essentially undergo routine blood donation processes such as donor history questionnaire, clinical examination, and testing for the infectious marker (serology and nucleic acid testing methods) along with ABO RhD grouping, antibody screening, and CBC. They will also undergo a test for IgG and IgM antibodies against SARS-CoV-2, which should be positive for IgG.

Data collection forms have been developed to collect data for CP donors, recipients, and controls (comparators).

### Response Assessment

The response assessment includes daily clinical assessment by a physician; vital signs including temperature, blood pressure, respiratory rate, and heart rate; oxygen saturation; oxygen requirement; ventilator requirement and the modes employed; inotrope medications requirement; CBCs, liver function tests, urea, creatinine, and electrolytes daily; Apache score; Sequential Organ Failure Assessment score; fluid balance; x-ray or CT changes, repeated every 3-5 days; organs functions assessment; plasma doses and frequency requirement; transfusion-related side effects including TRALI, TACO, etc; and the SARS-CoV-2 RNA will be tested on recovery (or deterioration to determine alternative etiology).

### Study Endpoint and Outcome Measures

Our primary endpoints are ICU (or designated area for critical patients) length of stay; safety of CP; and reporting of SAE such as anaphylaxis, TRALI, and TACO.

Our secondary endpoints will include number of days on mechanical ventilation, 30-day mortality, and days to clinical recovery as defined by the MOH.

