### Study Population

A total sample size of 575 patients, 115 CP recipients and 460 matched controls (1:4 ratio), will be sufficient to detect a clinically important difference of 11.6% between two groups (CP recipients vs matched controls) in 30-day mortality using a two-tailed *z* test of proportions and chi-square test with 80% power and a 5% level of significance. This 11.6% difference represents a 12.4% mortality in the CP recipient group and 24.4% mortality in the matched control patients [23].

The treatment group (CP recipients group) will have 115 patients who have COVID-19 but have not recovered yet as per the inclusion criteria. The control group (comparator group) will have 460 patients who are either not consenting to receive CP or those who will not be able to receive CP due to nonavailability to compare the efficacy of the CP. Control group patients will be subjected to propensity score (PS) matching based on age, gender, diabetes mellitus (DM), hypertension (HTN), and intubation.

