### Statistical Analysis

Descriptive and inferential statistics will be used to characterize the study sample and test the hypotheses. Descriptive results for all quantitative variables such as age will be presented as mean (SD; for normally distributed data) or median with interquartile range (for data not normally distributed), while numbers (percentage) will be reported for all qualitative variables such as gender.

To assess the independent effect of CP transfusion safety and survival, we will conduct a PS-matching (based on age, gender, DM, HTN, and intubation) analysis. Among the predictors, exact matching will be enforced to achieve the balance for all predictors between the plasma and control groups.

The bivariate analysis will be performed using independent sample *t* test, Mann-Whitney *U* test, Pearson chi-square test, or Fisher exact test whenever appropriate to compare the demographic characteristics (eg, age, gender, nationality) and clinical characteristics (improvement in oxygenation, laboratory parameters, radiological findings, complications, and length of hospital stay) between those who will receive the CP and those who will not receive this therapy.

The multiple binary logistic regression model will be used to assess the effect of CP transfusion on 30-day mortality after adjusting for potential confounding factors compared to matched controls patients. The adjusted odds ratio and 95% confidence interval for the adjusted odds ratio will be reported. The Hosmer-Lemeshow goodness-of-fit statistics will be used to determine whether the model adequately describes the data.

The time-to-event analysis will be measured from the date of diagnosis. The overall survival at 30 days and 3 months will be evaluated using the Kaplan-Meier estimator and compared between the two groups (plasma recipients vs matched control patients) using the log-rank test. A Cox proportional hazard model will also be used to estimate the hazard ratio for in-hospital 30-day mortality for the plasma group compared with matched control group patients after adjusting for potential confounding factors. In addition, interactions between CP administration and all the predictors will be tested to see if the plasma effects will be the same in subgroups. A *P*<.05 (two-tailed) will be considered statistically significant. All statistical analyses will be performed using SPSS version 24 (IBM Corp).

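### The primary efficacy endpoint is raw ICU length of stay with no rule for deaths, so a mortality difference can mask or reverse a true benefit or harm

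*Protocol article*

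**What the plan says.** Under Study Endpoint and Outcome Measures, the protocol article states "Our primary endpoints are ICU (or designated area for critical patients) length of stay". The other primary items concern safety, so ICU stay is the only primary measure of efficacy. Mortality stands apart: "Our secondary endpoints will include number of days on mechanical ventilation, 30-day mortality, and days to clinical recovery as defined by the MOH".

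Under Study Population, the trial is sized on 30-day mortality, with "12.4% mortality in the CP recipient group and 24.4% mortality in the matched control patients".

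Under Statistical Analysis, the only tests that could apply to a length of stay are the t test and the Mann-Whitney U test. The variable listed there is hospital stay, not ICU stay: "complications, and length of hospital stay) between those who will receive the CP and those who will not receive this therapy". Kaplan-Meier, log-rank and Cox methods are planned for survival and mortality only.

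No section attaches a death rule to ICU stay. There is no ICU-free-days definition, no worst rank for death, no time to discharge alive and no competing-event treatment.

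**The concern.** Death ends an ICU stay. On a raw duration, a patient who dies on day 3 scores better than one who leaves the unit well on day 14. That matters little where deaths are rare. Here the inclusion criteria admit patients with respiratory failure, septic shock or multiple organ failure, and the plan expects about one control in four to die and roughly half that proportion with CP. The design's own hypothesis is therefore that stay is cut short by death at different rates in the two groups.

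If deaths tend to precede survivors' discharge, a life-saving effect pushes the primary endpoint against CP and a harmful effect pushes it in CP's favour. The interim look at 40 recipients and 40 controls uses a similar analysis, and Time of the Study says that a benefit seen there would lead to a larger sample and a longer trial.

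Days on mechanical ventilation have the same weakness. Days to clinical recovery has a different one: it is undefined for a patient who dies, so death is a competing event there and does not produce a short value.

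**Working it through.** **Inputs from the article:** 30-day mortality 12.4% (CP) and 24.4% (control); 115 and 460 patients; two-sided 5% level; 80% power. **Assumed, because the article gives none:** mean ICU stay of survivors (S) and of decedents (D).

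**1. The plan's own figure.** The article states "A total sample size of 575 patients, 115 CP recipients and 460 matched controls (1:4 ratio") and "with 80% power and a 5% level of significance". With r = 4 and p̄ = (p₁ + r·p₂)/(1 + r):

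n₁ = [1.96·√((1 + 1/r)·p̄(1 − p̄)) + 0.84·√(p₁(1 − p₁) + p₂(1 − p₂)/r)]² / (p₁ − p₂)²

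- For 12.8% vs 24.4%, n₁ = 115 and n₂ = 460, with power 80.1%. The size reproduces.
- For the printed 12.4% vs 24.4%, n₁ = 107 and n₂ = 428 (117 and 468 with continuity correction). Power at 115/460 is 83.2%.

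The printed rates differ by 24.4 − 12.4 = 12.0 points, whereas the text says "will be sufficient to detect a clinically important difference of 11.6% between two groups". That is a separate matter. With 11.6 points, the shifts below shrink only slightly (0.116 × 7 = 0.81 and 0.116 × 4 = 0.46 days).

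**2. Shift in mean stay when CP changes mortality only.** In each group, mean stay = p·D + (1 − p)·S, with p the group's mortality. CP minus control is therefore (0.244 − 0.124)(S − D) = 0.12·(S − D).

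| S / D (days) | CP | Control | CP − control |
|---|---|---|---|
| 14 / 7 | 0.868 + 12.264 = 13.13 | 1.708 + 10.584 = 12.29 | +0.84 |
| 14 / 10 | 1.240 + 12.264 = 13.50 | 2.440 + 10.584 = 13.02 | +0.48 |
| 12 / 5 | 0.620 + 10.512 = 11.13 | 1.220 + 9.072 = 10.29 | +0.84 |
| 14 / 14 | 14.00 | 14.00 | 0 |
| 14 / 18 | 14.50 | 14.98 | −0.48 |

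**3. Harm.** Let CP raise mortality by the same 12 points, to 36.4%, at 14/7. CP mean = 0.364 × 7 + 0.636 × 14 = 11.45 against 12.29, so the harmful treatment looks 0.84 days better.

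**4. How often this reaches significance.** Simulation: 115 vs 460, gamma stays with shape 1.5, equal survivor stays, Mann-Whitney, 2,000 trials per setting, done twice with separate draws.

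| S / D | CP significantly longer | CP significantly shorter (one of the two sets) |
|---|---|---|
| 14 / 7 | 13.0%, 12.6% | 0.4% |
| 14 / 10 | 6.6%, 6.1% | 1.3% |
| 12 / 5 | 17.9%, 16.4% | 0.3% |

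Chance alone would give 2.5% in each direction. Under the harm scenario, a false benefit appears in 6% to 16% of trials. A lognormal model (log-SD 0.6, survivor median 12 days, 1,000 trials) gives CP significantly longer in about 34%, 19% and 10% for decedent medians of 4, 6 and 8 days. At equal medians of 12 days it gives about 2% in each direction.

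**5. If CP also shortens survivors' stay by a fraction f.** CP − control = 0.12·(S − D) − 0.876·f·S. This is zero at f = 0.84/12.264 = 6.8% (14/7), 0.48/12.264 = 3.9% (14/10) and 0.84/10.512 = 8.0% (12/5). At f = 10% the differences are 0.84 − 1.23 = −0.39, 0.48 − 1.23 = −0.75 and 0.84 − 1.05 = −0.21 days, and CP is significantly longer in only 1% to 2.5% of gamma trials. The survivors' true gain in those cases is 1.4, 1.4 and 1.2 days, so the endpoint shows only part of it.

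**The case against.** The strongest reply has four parts.

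- **The analysis is partly inferred.** The article names no test for ICU stay and does not say that an early death counts as a short stay. It is a condensed article, and an analysis plan could say more. This stands as a limit on wording: a reader might infer that the plan expressly scores early death as a good outcome, and it does not. But the endpoint itself is fixed as a raw duration. Moving to ICU-free days would change the endpoint, not supply a detail.
- **The direction is conditional.** A reader might infer that the plan's mortality hypothesis guarantees a wrong-signed result. It does not. That needs decedents to leave the ICU earlier than survivors and CP to do little for survivors' stay, and the article gives no data on either. This stands in full.
- **Mortality is visible anyway.** It is a named secondary endpoint, carries the sample size and has its own logistic, Kaplan-Meier, log-rank and Cox analyses. That would expose a conflict with ICU stay but would not repair the primary comparison.
- **The remedy is not only a change of wording.** Data Collection defines day 0 by CP infusion alone, which gives controls no starting day, and it does not list the ICU discharge date. Both points are correct and belong in the fix.

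**Conclusion.** The concern holds in conditional form. The sole primary efficacy measure is a duration that death cuts short, with no rule for deaths, in a trial that plans on 12.4% and 24.4% mortality. When deaths precede survivors' discharge, the comparison can hide or reverse a true benefit or harm.

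The mean shift is 0.12 times the survivor-decedent gap: 0.48 to 0.84 days under the assumed stays, with CP significantly worse in about 6% to 18% of trials if survivors' stay is unaffected. The shift is zero at equal stays and changes sign if decedents stay longer. A reduction of about 10% in survivors' stay more than offsets it, leaving a diluted benefit and not a reversed one. All stay lengths and distributions are assumptions.

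The conclusion does not rest on any one of them. The sign of the primary result depends in part on the timing of deaths, which the plan does not control, so the result cannot be read alone as benefit or harm.

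**What to change.** Define the primary efficacy endpoint in one of two ways:

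- ICU-free days alive to day 30, with death ranked worst, compared by a rank-based or proportional-odds analysis; or
- time to ICU discharge alive, with death as a competing event.

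State an index day that is defined the same way in both groups, for example ICU admission, or for each control a day matched to the recipient's infusion day. The matched day has the advantage of not counting time during which a recipient must, by definition, have been alive to receive plasma.

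Replace days on mechanical ventilation with ventilator-free days, and analyse time to clinical recovery with death as a competing event. Report raw ICU stay by vital status as description only. Name the ICU endpoint explicitly in Statistical Analysis, where only hospital stay now appears.

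Cost: revised endpoint and analysis wording, plus recording of ICU discharge and death dates and an index day for controls. A composite is somewhat less intuitive than days in ICU. If CP acts only on mortality, ICU-free days will behave much like a mortality comparison with less power than the planned one: in the gamma simulations it favoured CP significantly in about 50% to 53% of trials, against the planned 80%. Mortality should therefore still be reported beside it.
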